## Abstract

**Background:**

Patients with heart failure (HF) and colorectal cancer (CRC) are prone to comorbidity, a high rate of readmission, and complex healthcare needs. Self-care for people with HF and CRC after hospitalisation can be challenging, and patients may leave the hospital unprepared to self-manage their disease at home. eHealth solutions may be a beneficial tool to engage patients in self-care.

**Methods:**

A randomised controlled trial with an embedded evaluation of intervention engagement and cost-effectiveness will be conducted to investigate the effect of eHealth intervention after hospital discharge on the self-efficacy of self-care. Eligible patients with HF or CRC will be recruited before discharge from two Norwegian university hospitals. The intervention group will use a nurse-assisted intervention—eHealth@Hospital-2-Home—for six weeks. The intervention includes remote monitoring of vital signs; patients’ self-reports of symptoms, health and well-being; secure messaging between patients and hospital-based nurse navigators; and access to specific HF and CRC health-related information. The control group will receive routine care. Data collection will take place before the intervention (baseline), at the end of the intervention (Post-1), and at six months (Post-2). The primary outcome will be self-efficacy in self-care. The secondary outcomes will include measures of burden of treatment, health-related quality of life and 30- and 90-day readmissions. Sub-study analyses are planned in the HF patient population with primary outcomes of self-care behaviour and secondary outcomes of medication adherence, and readmission at 30 days, 90 days and 6 months. Patients’ and nurse navigators’ engagement and experiences with the eHealth intervention and cost-effectiveness will be investigated. Data will be analysed according to intention-to-treat principles. Qualitative data will be analysed using thematic analysis.

**Discussion:**

This protocol will examine the effects of the eHealth@ Hospital-2-Home intervention on self-care in two prevalent patient groups, HF and CRC. It will allow the exploration of a generic framework for an eHealth intervention after hospital discharge, which could be adapted to other patient groups, upscaled, and implemented into clinical practice.

**Trial registration:**

Clinical trials.gov (ID 301472).

## Background

Worldwide healthcare systems are increasingly relying on patients to manage their treatment and illness through self-care due to the rising rates and pressures created by chronic illness [1, 2]. In Norway and globally, cancer and cardiovascular conditions are illnesses with considerable burdens for patients and healthcare costs [3]. In 2020, approximately 15,000 Norwegians were diagnosed with heart failure (HF) [4] with the prevalence of known HF being 1–2% of the global population [5]. In 2020, nearly 4,500 Norwegians were diagnosed with colorectal cancer (CRC) with the prevalence increasing by 1.8% per year in Norway between 2012 and 2016 [6]. Both conditions are prone to comorbidity and complex healthcare needs, including high readmission rates [5, 7–9].

While the two illnesses are different in terms of diagnosis, treatment, prognosis and trajectory [10, 11], HF and CRC have similar needs for follow-up care and the development of patients’ self-care skills [12, 13]. Individuals with either HF or CRC have challenges with unmet health needs and limited access to healthcare professionals, particularly after hospitalisation [14–16]. Between hospital admissions and specialist appointments, patients must self-care at home [17]. Patients also often receive limited support with the transition from hospital to home [18]. Inadequate follow-up of HF and CRC patients after hospitalisation can potentially result in unsafe and anxious patients [16, 19], which may lead to poor adherence to medical treatment and self-care tasks [20], resulting in readmission [21] and low quality of life [22]. Unsupportive healthcare service pathways lead to a higher burden of treatment [23].

The burden of treatment is the delicate balance between a patient’s capacity (capability and resources) and the workload (tasks required by illness management and treatments) [24]. If that balance tips so the workload exceeds the patient’s capacity, patients experience poorer outcomes, health-related quality of life (HRQoL) [25] and self-care [24]. Self-care refers to ‘the ability of the patient to deal with a chronic illness including symptoms, treatment, physical and social consequences, and lifestyle changes’ [26]. It is a complex construct with multiple processes and influencing factors [27]. Self-efficacy is key to influencing patient decisions around self-care behaviours [27]. It refers to an individual’s confidence in their capacity to act in the ways necessary to reach specific goals [28] and is linked to self-management [1].

eHealth solutions may provide a way to support self-care in illnesses such as HF and CRC. eHealth is both the delivery of health services and information [29] as well as the conceptualisation of user interactions with the technology (e.g., monitoring of vital signs, communication with healthcare providers and utilisation of data to restore health) [30]. Patients who use eHealth may be more motivated to engage in self-care behaviours [31, 32]. eHealth-based self-care interventions have been found to improve confidence in self-care of cancer patients and coronary heart disease patients [33, 34]. Within HF, a review of eHealth follow-up programmes has reported significantly increased HRQoL, but the impact on readmissions and self-care is less clear [35]. In cancer survivors, Chan et al. [36] reported that telemedicine significantly improved HRQoL and symptom burden. A cost-effectiveness review suggested that nurse-assisted follow-up is a promising method for reducing costs (compared with rehospitalisation) without endangering patient outcomes, following cancer treatment [37].

Research on how eHealth can best support patients with HF and CRC during the period after hospital discharge is sparse [36, 38]. Therefore, a nurse-assisted eHealth intervention eHealth@Hospital-2-Home was developed and tested based on a body of research in HF and CRC patients [15, 35, 39, 40]. Existing software and application technology—the Dignio Connected Care [41]—was selected as the platform for the intervention. The eHealth intervention includes:monitoring of vital signs using connected technology (heart rate, blood pressure, pulse oximetry, temperature, weight)patient self-reporting of symptoms, health and well-beingsecure messaging between patients and hospital-based nurse navigators when patients’ vital signs exceed the acceptable rangeaccess to HF and CRC health-related educational information.

This paper presents the protocol for a randomised controlled trial (RCT) evaluating a complex intervention [42] to study the effects of the eHealth@Hospital-2-Home intervention on the primary outcome of self-efficacy in self-care in HF and CRC patients. The protocol was informed by the preliminary results from a feasibility study with the two patient groups [43] and follows the recommendations for protocol items for a clinical trial (SPIRIT) checklist [44] and the CONSORT checklist for reporting items of a randomised trial [45].

The aims of the RCT are as follows.

Primary aims:1) To evaluate the immediate (Post-1: 6 weeks) and extended effects (Post-2: 6 months) of an eHealth intervention after hospital discharge to improve patients’ self-efficacy to self-manage chronic illness. We hypothesise that participants in the intervention group will report higher levels of self-efficacy at six weeks after hospital discharge and at six months after baseline compared with the control group.

Secondary aims:2) To investigate the effects of the intervention on the secondary outcomes of the burden of treatment, HRQoL, perceived collaboration and social support from healthcare personnel, healthcare utilisation and 30- and 90-day readmission rates in the two patient groups.3) HF sub-study: To investigate the effects of the intervention on self-care behaviour, medication compliance and 6- and 12-month readmissions in participants with HF only. We hypothesise that the HF intervention group will report higher levels of self-care behaviours, better medication compliance and reduced 6- and 12-month hospital readmissions compared with the HF control group.

Explorative aim:4) To evaluate patients’ and nurse navigators’ engagement and experiences with the eHealth intervention and estimate cost-effectiveness. Evaluation will use mixed methods [42].

The logic model for the intervention [46] and RCT (see Fig. 1) illustrates the resources needed (i.e., intervention) to implement change (i.e., mechanisms of change) that may lead to the result we intend to achieve (i.e., outcomes).

**Fig. 1 Fig1:**
[figure not shown]
Logic model of the eHealth@Hospital-2-Home intervention

## Methods

### Study design and setting

This study is an RCT with an embedded evaluation of intervention engagement and cost-effectiveness. The RCT is part of a larger study ‘Nurse-assisted eHealth service from the hospital to home: Ameliorating the burden of treatment among patients with noncommunicable diseases’ funded by the Norwegian Research Council (Funding No. 301472). An overview of the trial design is shown in Fig. 2.

**Fig. 2 Fig2:**
[figure not shown]
Overview of the RCT trial design

The trial will include study participants with HF and CRC from two similar-sized university hospitals in Norway (Study Sites A and B). Study Site A is a university hospital in the western part of Norway that provides specialist health care for approximately 370,000 inhabitants. Study Site B is a university hospital in the middle of Norway, providing specialist health care for approximately 300,000 inhabitants (as of September 2023).

### Eligibility of study participants

Eligible patients will be adults aged ≥ 18 years with either HF or CRC chronic illness admitted to the hospital, and able to speak and write in Norwegian. See Table 1 for detailed illness-specific eligibility criteria.

**Table 1 Tab1:** Eligibility criteria

	**Heart failure**	**Colorectal cancer**
**Inclusion**	• Inpatient with symptomatic HF • Decompensation symptoms such as dyspnoea at rest, pulmonary congestion (X-ray, oedema, or positive rales on auscultation) and elevated NT-proBNP > 1000 pg/mL	Surgically treated for cure stage I–III colon or rectal cancer [47]
**Exclusion**	• Waiting list for a heart transplant • Requires LVAD • Life expectancy < 6 months	• Metastatic cancer • Clavien-Dindo Surgical Complication Score > 3a [48] • Life-threatening acute medical emergencies (e.g., myocardial infarction)
	• Severe mental illness or cognitive impairment • Planned discharge to a nursing home • Participation in other intervention studies • Unable to stand independently	

*HF* Heart failure, *LVAD* Left ventricular device, *NT-proBNP* N-terminal pro b-type natriuretic peptide

### Sample size calculations

The sample size goal is 240 patients (HF = 180, CRC = 60) equally divided between the intervention and control group. Assuming a 20% dropout, a sample size of 240 will provide a power of 80% to detect, at an α error probability of < 0.05, a medium-sized standardised difference in the primary outcome (self-efficacy for managing chronic disease) of 0.4 in the disease groups combined at the first time point (Post-1). For the HF sub-study, assuming the same dropout rate of 20%, there will be 80% power to detect a standardised effect of size 0.5 for the outcome of self-reported self-care.

### Patient screening and recruitment

All patients will be screened and recruited during their hospital admission. Patients with HF will be recruited from both sites, whereas those with CRC will be recruited from a surgical ward at Study Site A. Hospital ward patient lists will be screened by the nurse navigators daily for eligible patients using the eligibility criteria (see Table 1). Nurse navigators will approach those who are eligible, providing written and oral study information. A short, animated video about the research project and the nurse-assisted eHealth intervention will be provided for viewing [49]. The patient will be included if informed written consent has been provided.

### Randomisation

Patients who agree to participate will be randomised. Randomisation occurs after the patients have completed the baseline assessment. Participants will be allocated by stratified block randomisation (1:1) to either the intervention or control group using sequentially numbered, opaque, sealed envelopes. Stratification will occur by diagnostic groups (HF and CRC) and study sites. Separate randomisation lists will be produced for all three strata by a statistician [name] and concealed from researchers. Randomisation allocation will be blinded for statisticians and researchers performing the data analyses.

### Intervention group: eHealth@Hospital-2-Home intervention

The eHealth intervention is a non-acute, alert- and communication-based service operated by nurse navigators. The intervention duration is six weeks following hospital discharge and aims to monitor and support participants.

#### Participants

Participants in this group will be issued an iPad with only the eHealth application MyDignio. MyDignio uses a cloud-based secure database that can be accessed without an IP address, allowing information exchange using an encrypted message exchange system. Communication via chat and video links between the patients and the nurse navigators in the hospital is supported in the application. MyDignio app is linked to monitoring devices by Bluetooth for each participant to record clinical measures (i.e., blood pressure, pulse, temperature and weight).

Participants will be asked to register clinical measurements HF and CRC daily, register symptoms daily and weekly, and register well-being daily (see Table 2 for overview) into MyDignio app, which will be monitored by nurse navigators employed at the two hospitals [41]. Participants are asked to perform the clinical measurements at approximately the same time to minimise daily variance caused by meals, fluid intake and bowel movements. They will receive a reminder in the system if they have not reported the data. Additionally, participants can communicate with the nurse navigator at any time via chat and video links through the application. Before discharge from the hospital, participants will receive training from the nurse navigators on the use of MyDignio app and the monitoring devices. Instructions and contact details for accessing technical support will be provided.

**Table 2 Tab2:** Clinical measurements, symptoms and well-being reported by participants

	**Heart failure**	**Colorectal cancer**
**Daily clinical measurements**		
Body weight	x	x
Temperature 10 days		x
Blood pressure and pulse	x	
**Daily self-reports**		
Well-being	x	x
Side effects of medications	x	
Shortness of breath	x	
Heart failure symptoms	x	
Dizziness and oedema	x	
Nausea, diarrhoea		x
Bowel function		x
Redness and pain in surgical wound		x
**Weekly self-reports**		
Perceived side effects of medications	x	
Appetite	x	x
Fluid intake		x
Energy and activity level	x	x
Influence of disease on everyday life	x	
Sleep	x	x
Anxiety and negative thoughts		x
Sadness and loneliness	x	x

#### Nurse navigators

Eight registered nurses will be recruited as nurse navigators to work either with HF (nurse navigators = 4) or CRC (nurse navigators = 4). The nurse navigators are experienced hospital nurses with the clinical skills required to identify and monitor high-needs patients. Digital and in-person training (13 h) is provided in the study procedures and using DignioPrevent.

DignioPrevent is the clinical interface to the eHealth intervention application. Nurse navigators use DignioPrevent to monitor and respond to participant data. They will contact participants 24 to 48 h after their hospital discharge to offer further support in using the MyDignio app. Nurse navigators also monitor participants using DignioPrevent to respond to messages daily and schedule calls. The private messaging system in DignioPrevent allows nurse navigators to answer questions about the patient’s health and provide feedback and advice to the participants about medications, nutrition, fluid intake and activity based on the participant-reported data, facilitating informed and supportive self-care. Nurse navigators can also provide information about available websites with information about HF and CRC, resources and peer support services relevant to the patient’s situation.

Each participant profile will have personalised predefined thresholds that trigger green, yellow or red flags. Yellow and red flags require the nurse navigator to respond to those patients within 48 h. Red flags require the nurse navigator to advise the patient to first conduct extra clinical measures to ensure that they are correct; and second, advise the patient to contact their general practitioner or the municipal emergency department to ensure proper treatment, as the intervention is not an emergency service. Nurse navigators can consult with the medical doctor or surgeon collaborating with the research project to provide medical oversight for the trial about possible medical interventions. The intervention group is considered low risk to participants and provides more support than routine care. Actions to mitigate participant risk include setting specific clinical thresholds on all patient-inputted data, providing research-specific training and provisioning technical support.

### Control group: routine care

The control group will only receive routine care. Routine care refers to the standard care offered after hospital discharge. For all participants in this group, this includes written discharge information, information on how to schedule a follow-up appointment at the hospital outpatient clinic or with their general practitioner if needed, and information to contact their general practitioner or municipal emergency department if worrying symptoms occur after hospital discharge. The participants will receive pertinent disease-specific information as part of routine care for both patient groups. To support participants in this group, they will be contacted by telephone between Post-1 and Post-2 to confirm their continuous participation in the trial and to offer any additional support as required.

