### Ancillary and post-trial care

All participants who were surgically treated for CRC will, as part of standard care, attend a post-surgical follow-up appointment at the gastrosurgical outpatient clinic and systematic follow-up according to national guidelines. Patients with HF will be followed up by their general practitioner or at an HF outpatient clinic. All participants will receive a follow-up call when the study is complete with information that the study has ended, how they can access information about trial results and to ask if they have feedback to provide to the research team.

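### Controls, and as described only controls, get a trial support call between Post-1 and Post-2; this conflicts with routine care only and can bias the six-month comparison, though not the main one at Post-1

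*Protocol article*

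**What the plan says.** All of this is in the Protocol article.

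- **Comparator.** *Control group: routine care* opens with "The control group will only receive routine care" and defines the term: "Routine care refers to the standard care offered after hospital discharge". The components listed are discharge information, how to arrange follow-up, whom to contact about worrying symptoms, and disease-specific information. No trial telephone call is among them.
- **The added call.** The same paragraph ends with one: "To support participants in this group, they will be contacted by telephone". Its timing and purpose follow, and controls are to be "contacted by telephone between Post-1 and Post-2 to confirm their continuous participation in the trial and to offer any additional support" if they need it.
- **The other arm.** In *Intervention group: eHealth@Hospital-2-Home intervention*: "The intervention duration is six weeks following hospital discharge and aims to monitor and support participants". The nurse contacts described under *Nurse navigators* belong to that period. The only call described for both arms is in *Ancillary and post-trial care*: "All participants will receive a follow-up call when the study is complete".
- **Role of Post-2.** The primary aim in *Background* is to "evaluate the immediate (Post-1: 6 weeks) and extended effects (Post-2: 6 months) of an eHealth intervention". *Statistical methods* puts both post-intervention scores in the primary model, with an interaction between occasion and group, and names Post-1 as the main comparison.

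**The concern.** The comparator is described in two ways that cannot both be true. If controls receive only what the hospital and primary care normally offer, there is no trial call. If there is a trial call whose stated purpose is support, the Post-2 comparator is routine care plus that call.

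The call falls between the two outcome measurements and, as described, in one arm only. The primary outcome is self-reported confidence in managing illness, and participants know whether they were given the app, so a personal offer of support could plausibly move it. If the difference between arms narrows from Post-1 to Post-2, the planned interaction cannot tell a fading intervention effect from help given to controls. The call is also a retention contact, so it may change who still answers at Post-2 in one arm and not in the other.

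**Working it through.** **1. Contacts by arm, as described.**

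| Period | Intervention | Control |
|---|---|---|
| Discharge to Post-1 | nurse navigator contact (the intervention) | routine care |
| Post-1 to Post-2 | no trial contact described | telephone call: participation and offer of support |
| After study completion | follow-up call | follow-up call |

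The first row is the treatment contrast and the last row comes too late to matter. The middle row is the unplanned difference. That the intervention arm gets no such call is inferred from silence, supported by wording that ties the call to the control group.

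**2. Which outcomes can be touched.** Post-1 is at 6 × 7 = 42 days after discharge. Counting readmission windows from discharge (an assumption):

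- Post-1 self-efficacy and 30-day readmission: complete before the call (30 < 42). Not affected.
- 90-day readmission: 90 − 42 = 48 days lie after Post-1. Exposed only if the call comes before day 90, and the date is not given.
- HF readmission to 6 months, days alive and out of hospital to Post-2, and Post-2 cost-effectiveness: exposed for the part of the window after the call.
- Post-2 self-efficacy and the time-by-group interaction: fully after the call. Exposed.

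**3. The plan's own power figure.** Inputs from *Sample size calculations*: 240 patients, 1:1, 20% dropout, standardised difference 0.4, α = 0.05 (two-sided assumed), 80% power, at Post-1.

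- Evaluable per arm: 240 × 0.8 / 2 = 96.
- Power ≈ Φ(d × √(n/2) − 1.96) = Φ(0.4 × √48 − 1.96) = Φ(2.771 − 1.960) = Φ(0.811) = 79.1%. The t-test version gives 78.7%.

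The stated 80% is reproduced. It refers to Post-1, so the call does not change it.

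**4. Illustration at Post-2.** The documents give neither a Post-2 effect nor an effect of the call. Assume a true Post-2 difference of 0.4 SD, 96 evaluable per arm (both carried over from Post-1), an unadjusted two-sided test, and a gain g in controls from the call. The observed difference is then 0.4 − g.

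| g (SD) | Difference (SD) | Difference × √48 − 1.96 | Power |
|---|---|---|---|
| 0 | 0.40 | 0.811 | 79% |
| 0.05 | 0.35 | 0.465 | 68% |
| 0.10 | 0.30 | 0.118 | 55% |
| 0.15 | 0.25 | −0.228 | 41% |
| 0.20 | 0.20 | −0.574 | 28% |

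If the call does nothing to outcomes, nothing is lost.

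**5. Dropout.** A likelihood-based mixed model does not need equal retention in the arms. It needs missingness to depend only on observed data, and *Statistical methods* includes group, baseline score and important predictors of dropout. Bias remains only if the call changes dropout in a way that depends on unobserved values. The documents do not show whether it would.

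**The case against.** The strongest defence is that the trial's main question is settled before the call is made. The main comparison and the power statement are both at Post-1, and no power is claimed for Post-2. That stands, and it limits how serious the point can be.

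It can also be said that the call may be trivial. The caller, content, intensity and date are not given, support is offered only as needed, and it might mean no more than help with taking part. This is fair as to size. It does not remove the conflict in wording, because the paragraph gives support as the reason for the call.

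A third argument is that a condensed article may simply omit a matching call to the intervention arm. That is possible. If so, one sentence settles it.

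Three stronger readings are tempting, and the documents do not support them:

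- A reader might infer that every outcome after Post-1 is biased. The text shows only that bias is possible, and outcomes are exposed unequally.
- A reader might take 55% as the power at Post-2. It is one row of an assumed range in an unadjusted test, whereas the planned analysis adjusts for baseline.
- A reader might conclude that unequal retention invalidates the mixed model. It does not, for the reason in step 5. A control-only call could even reduce an imbalance in dropout if controls would otherwise leave more often.

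**Conclusion.** The point holds in limited form. The description of the control condition contradicts itself and, as written, creates an avoidable difference between arms before Post-2. The extended-effect part of the primary aim, the time-by-group interaction and the outcomes that run past the call are open to bias. The Post-1 comparison, the sample-size statement and 30-day readmission are not.

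The likely direction is toward no difference, because useful support would raise control scores. Differential retention leaves that uncertain. The size is unknown: under the assumptions in step 4, the power loss at Post-2 runs from none (no effect of the call) to about 51 percentage points (79% to 28%, for a gain of 0.20 SD). The conclusion assumes that no matching call to the intervention arm exists. The change is worth making because it is cheap and part of the primary aim is exposed, but it does not threaten the trial's main result.

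**What to change.** 1. Reconcile the two statements in *Control group: routine care*, and state explicitly whether the intervention arm is contacted between Post-1 and Post-2.
2. Use one contact for both arms in that interval, with the same timing and script, limited to confirming participation. The route must also reach those who chose postal questionnaires, so a purely electronic reminder would not clearly be enough.
3. Recruitment began in May 2023, so log the control calls already made, with date and any support given.
4. Report retention by arm at Post-1 and Post-2, and describe the Post-2 comparator as what controls actually received.

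The cost is a procedural amendment and brief contacts with up to 120 intervention participants (240 / 2). The drawback is that controls enrolled before and after the change may differ in the contact they received. The log lets that be described.
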